### Study design

The design of this project comprises different dentitions (primary and permanent teeth) and different surfaces (single or multiple-surface).

This is a pragmatic, two-arm, parallel group, patient-randomized trial which has 10 dentists as operators in dental offices located at public schools. The schedule of enrolment, interventions, and assessments diagram is showed in Fig. 1.

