### Organization intervention/Operators

The operators of this study will be 10 dentists who work in the dental offices located at the public schools of Barueri. All operators will receive only a guideline of how to prepare, restore and finalize the restoration according to the original procedures of ART [2]. Regarding the procedures in the CT group, all the dentists will receive explanations about the preparation of the cavity according to partial caries removal philosophy and also about the manufactures’ specifications of the materials used. Since it is a pragmatic clinical trial, operators with different clinical expertise will be selected and no training will be performed for both groups.

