### Randomization

The randomization lists were computer generated (www.randomization.com), based on randomly permuted blocks of varying size (2, 4 or 6, randomly sampled with equal probability) and stratified for operator (1–10), dentition (primary/permanent) and surface (single/multiple). Opaque, sealed and sequentially numbered envelopes will be used to randomize the participants into the treatment groups (ART and CT).

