### Outcomes

As a pragmatic trial, the outcomes must be relevant to the patient. So, the primary outcome of this study is the longevity of single and multiple-surfaces ART-restorations compared to Conventional Treatment (CT) in primary and permanent molars.

As secondary outcomes we will evaluate the technical preference assessment by dentists using an adapted and translated questionnaire [3] (Additional file 3) and the evaluation of the cost-effectiveness of the two techniques applied. The longevity of the tooth, in case of primary teeth will also be evaluated.(I)Longevity of the restorationTreatment longevity will be evaluated after 6, 12, 18 and 24 months by one trained and calibrated examiner. The intra-examiner and inter-examiner agreement will be calculated using the Cohen’s Kappa test and only scores above 0.7 will be accepted.Following on the Roeleveld et al. [16] criteria, it will be considered “success” only the restorations that receive the scores 00 and 10. The scores 11–40 will be considered “failure”. The scores 50, 60, 70 and 90 will not be assessed in the analysis of the success of the restoration.(II)Longevity of the toothThis outcome will be calculated only for the primary teeth included in this research. Intact restorations and the ones with a minor failure of the restoration (scores 00 to 30) will be considered as “success”, using the same criteria mentioned above [16]. Only the restored teeth that presents symptoms of pulp inflammation or need extraction (scores 40 and 50) will be considered as “failure”, since it cannot be considered as a successful treatment for the tooth.The main objective of a restoration is to provide a better condition for the patient by improving oral hygiene, inactivating the caries process, and returning the masticatory function of that tooth, so the scores considered “minor failures” will not be considered failure for the tooth [17].(III)Cost-effectivenessTo calculate the direct and indirect costs of the procedures, it will be taken into account the time spent on each treatment, including the treatment and the follow-up visits. The reference group to do the cost analysis will be the ART. The time spent in each session will be timed by a dental assistant (which is not participating in diagnostic tests or treatment) in order to input the cost-effectiveness analysis of the methods used in the research. All the information will be registered in predetermined sheets the specifications and quantity of all materials used.For the calculation of direct costs, it will also be considered the prices of materials used in each procedure based on an actual dental market value converted in US Dollars and obtained by the mean values from different dental stores for the referred products. In order to calculate the Professional Cost, we will calculate the time spent in each session and convert it in hours and multiply it by the medium income of the dentist per hour as related by the Brazilian Ministry of Labor and Employment ($36.23).To estimate the procedure cost, it will be considered both variable cost, which includes electricity and equipment depreciation, and material costs [18, 19]. To calculate the equipment depreciation (peripherals, dental chair and instrumental), we will consider their costs, the life span of five years and a monthly use of 160 h, using an estimate value per hour of $1.81.(IV)Preference of the treatments by dentistsThe preference of dentists will be evaluated at the end of the operative phase. Thus, we aim to identify which is the preferred procedure by professionals. To evaluate this outcome, a questionnaire composed of six items will be applied.This questionnaire was adapted from the study of Pani et al. [3], which evaluated the preference of students with respect to composite and silver amalgam. The questionnaire was translated from English to Portuguese by a Brazilian dentist who is fluent in both languages and was adapted for comparing the composite resin and the glass ionomer cement used according to the ART. This questionnaire will be administered before and after the research for the dentists (Additional file 3).

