
### Data analysis

Data will be analyzed according to the protocol principle. First, to compare treatments’ and teeth longevity, both Kaplan-Meier survival analysis and Log-rank test will be applied. The association between restoration longevity and caries experience or type of cavity will be evaluated using Cox Regression.

As we have a cluster-effect related to the numbers of operators of this trial and its contextual variables (such as age, work experience and technique preference), the average event rates in the two groups over the two year study period will be then modelled and compared with a “shared frailty” model. This model is an extension of the Cox proportional hazard model that includes a frailty term (a statistical expression for random effect, unrelated to the clinical concept of frailty) to take dependency of events within a contextual (correlation between different falls by the same operator) into account. All participants will be included in the model until their last time point, which means that the model will use all available data right up to the time of withdrawal or trial completion. For each outcome, we will present the hazard ratios and 95 % confidence intervals for the intervention, adjusted by operator.

The variance analysis will be used to compare groups in relation to the cost after determining data normality through the Kolmogorov-Smirnov test. Poisson analysis will be used to assess the association between the treatment group, the preference of professionals and the cost of treatments. The significance level will be set in 5 %.

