**Fig. 2 Fig2:**
[figure not shown]
PRECIS domains diagram

As a pragmatic study, the conditions reported in this protocol are similar to those in real dental practice and the operators are dentists who work for the public health system. The decision to not perform any training for the operators is to maintain a closer representation of the dentists’ reality in dental practice, since they have different backgrounds of undergraduate learning. In that way, the operators only will receive one guideline on how to prepare, restore and finalize the restoration according to the original procedures of ART [2]. Regarding the procedures performed in the CT group, as all the dentists are used to do composite resin in their daily clinical practice, they will receive only some information about the manufacturer specifications for using these new materials. Due the evident differences between the techniques and materials used in each group presented in this trial, it is not possible to blind the patients, operators or evaluators.

Few clinical studies are reported in the literature using a bulk fill composite resin [9, 20] and to the best of our knowledge this is the first study to use this material also for restoring primary teeth. As this material can be used in a single increment until 4 mm allied to the use of a universal adhesive, which allows the self-etch technique, the clinical time may be shortened, reducing the contamination probability. As no rubber dam is available in public health dental practice in Brazil, the use of these materials could be an answer to improve the conventional treatment longevity.

In cases where the child has more than one eligible cavity in the same dentition and surface (for example: two single-surface cavities in a primary molar in the same child), only one cavity will be randomly selected. In case of different teeth (permanent and primary) or different surfaces (single or multiple-surface), more than one tooth can be selected for the research, since the analysis of each group will be done separately (for example: one single-surface in a primary molar and one single surface in a permanent molar in the same child). In this case, each tooth will be randomly allocated to the intervention group since the analyses are going to be done separately according to dentition and surface.

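### The cost comparison names no operator term, although operator is a randomisation stratum and a likely source of cost variation; adding it is a free gain in precision for a secondary outcome

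*Protocol article*

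**What the plan says.** The Data analysis section gives cost one comparative method: "The variance analysis will be used to compare groups in relation to the cost after determining data normality", with normality judged by the Kolmogorov-Smirnov test. The comparison is between groups, and no other model term is named. A further sentence there plans a Poisson analysis linking treatment group, professionals' preference and cost.

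Elsewhere the article treats operator as important:

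- Study design: a "two-arm, parallel group, patient-randomized trial which has 10 dentists as operators".
- Randomization: permuted blocks of 2, 4 or 6, "stratified for operator (1–10), dentition (primary/permanent) and surface (single/multiple". Each dentist therefore treats teeth in both arms, in near balance.
- Organization intervention/Operators: "operators with different clinical expertise will be selected and no training will be performed for both groups".
- Data analysis, on the shared frailty model: "For each outcome, we will present the hazard ratios and 95 % confidence intervals for the intervention, adjusted by operator". As worded, this covers time-to-event outcomes, not cost.

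For professional cost, the Outcomes section (item III) will "calculate the time spent in each session and convert it in hours and multiply it by the medium income of the dentist per hour", at a fixed $36.23. Equipment depreciation is also charged by the hour, at $1.81. On strata, the Discussion says that "the analyses are going to be done separately according to dentition and surface".

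**The concern.** Balanced blocks within each dentist largely remove a dentist's general speed from the arm difference: a slow dentist is slow in both arms, and the effect cancels. An analysis by arm alone does not use this. It leaves the variation between dentists in its error term and so reports less precision than the design has delivered.

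Cost is where this is most plausible. Every timed hour carries $36.23 + $1.81 = $38.04 whoever works it, so differences in working speed pass straight into cost. Cost also matters to the trial's message. The abstract expects similar effectiveness and superior cost-effectiveness for ART, so cost is the component expected to separate the arms.

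**Working it through.** **Inputs from the protocol.** There are 10 operators; blocks of 2, 4 or 6 within operator, dentition and surface; groups of 304, 278, 304 and 328 teeth (Table 1); and a two-sided 5 % level. No standard deviation, effect size, operator variance or power is given for cost, so there is no stated cost figure to reproduce.

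**The only operator figure.** The sample size is raised by 40 % for operator clustering. Read as a design effect, 1 + (m − 1) × ICC = 1.4:

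- With final group sizes, m = 27.8 to 32.8 teeth per operator, so ICC = 0.4/26.8 = 0.015 down to 0.4/31.8 = 0.013.
- With sizes before inflation (165 to 195), m = 16.5 to 19.5, so ICC = 0.4/15.5 = 0.026 down to 0.4/18.5 = 0.022.

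This ICC concerns survival, not chair time. It does not settle ρ for cost, but it is a reason to include small values in the range.

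**Case 1: operators shift cost equally in both arms.** Set total cost variance to 1, with share ρ between operators, and N teeth split 1:1 within operator.

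- Standard error from the arm-only analysis: √(4/N).
- True standard deviation of the arm difference: √(4(1 − ρ)/N).
- Ratio: 1/√(1 − ρ).
- Actual type I error: 2[1 − Φ(1.96/√(1 − ρ))].
- Power, if the adjusted analysis has 80 %: Φ(2.80 − 1.96/√(1 − ρ)), where 2.80 = 1.96 + 0.84.

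| ρ (assumed) | SE excess | Type I error | Power unadjusted |
|---|---|---|---|
| 0.01 | 0.5 % | 4.9 % | 79.7 % |
| 0.05 | 2.6 % | 4.4 % | 78.5 % |
| 0.10 | 5.4 % | 3.9 % | 76.9 % |
| 0.20 | 11.8 % | 2.8 % | 72.9 % |
| 0.30 | 19.5 % | 1.9 % | 67.7 % |

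Worked line for ρ = 0.20: 1/√0.80 = 1.118; 1.96 × 1.118 = 2.19; Φ(2.80 − 2.19) = Φ(0.61) = 0.73.

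A simulation of one group (10 operators × 30 teeth, the planned blocks, 2,000 runs per setting) shows the same pattern. At ρ = 0.20 with no arm difference, the unadjusted standard error averaged 0.114, the adjusted one 0.103, and the actual standard deviation of the estimate was 0.103. Simulated unadjusted power was 79.2 / 77.0 / 74.3 / 69.4 % at ρ = 0.05 / 0.10 / 0.20 / 0.30. With only ten operators the simulated loss at ρ of 0.20 and 0.30 is slightly smaller than the formula gives.

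**Case 2: the arm difference varies between operators.** Let it vary with variance τ² and treat operators as random. The variance of the estimate becomes 4(1 − ρ)/N + τ²/10. With ρ = 0.10 and N = 300, the first term is 0.012.

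- τ² = 0.05: √(0.012 + 0.005) = 0.130, against a reported unadjusted standard error of 0.115. Simulated type I error was 7.5 % unadjusted and 8.9 % with a fixed operator term.
- τ² = 0.10: √(0.012 + 0.010) = 0.148, against 0.116. Simulated type I error was 13.0 % and 14.5 %.

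Here the unadjusted standard error is too small, and a fixed operator term alone does not help.

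**The case against.** The strongest reply is that a one-sentence summary in an article does not exclude operator. Analysis of variance can carry several factors, and model terms for a secondary outcome are often left to a fuller plan. It is right that the article nowhere says operator is left out, and a reader should not infer a deliberate exclusion. But a method is stated, its comparison is between groups, and the paragraph before it takes care to adjust the hazard ratios by operator. Followed as written, the cost analysis lacks the term.

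The planned Poisson analysis brings in professionals' preference, which is an operator-level variable. It is a separate analysis and does not adjust the group comparison of cost.

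The size is also open to challenge. Both ρ and the 80 % baseline are assumptions. The protocol's 80 % belongs to the log-rank test, and if the cost difference is large relative to its spread the power loss is trivial. At the ICC implied by the 40 % inflation (0.013 to 0.026), the standard error excess is about 1 % and the power loss under one percentage point. This stands, and the table therefore starts at 0.01.

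Two stronger readings are tempting. A reader might infer that cost is pooled over dentition and surface, so that those differences swell the error term as well. The Discussion says the analyses are separate by dentition and surface, so operator is the only stratum at issue. A reader might also infer that the test must be conservative. That needs operators to act alike in both arms. The dentists use composite daily, receive only a guideline for ART, and may choose drill or hand instruments in the conventional arm, so Case 2 cannot be ruled out.

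**Conclusion.** The point holds as a free improvement to a secondary outcome. The stated cost comparison does not use a factor by which the trial randomises and which plausibly drives cost.

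If operators shift cost similarly in both arms, the estimated difference is unbiased and only precision is lost: from about 0.5 % on the standard error at ρ = 0.01 to about 20 % at ρ = 0.30, with power falling from an assumed 80 % to between 79.7 % and 67.7 %. The documents do not say where in that range the trial lies. If the arm difference varies between operators and they are regarded as random, the error runs the other way, and the remedy must go beyond a fixed operator term. Nothing here touches the log-rank comparison of longevity.

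**What to change.** In the Data analysis section, replace the cost sentence with a statement to this effect: within each dentition-by-surface group, cost will be compared by a linear model (or a generalised linear model if cost is skewed) with arm and operator as terms, and the adjusted mean cost difference in US dollars will be reported with its 95 % interval. Add that variation of the arm difference between operators will be examined as a sensitivity analysis, for example with a random operator-by-arm term.

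The cost is wording only. Operator is already known for every tooth as a randomisation stratum, and the term uses 9 degrees of freedom in groups of 278 to 328 planned teeth.

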In order to evaluate the preferences of dentists and measure a professional-centered outcome, a questionnaire composed of sixteen items will be applied [3]. It aims to evaluate factors influencing dentists’ preference of amalgam or composite for posterior dental restorations, which can influence the quality of the restorations.

The growing use of cost-effectiveness analysis (CEA) to evaluate the costs and health effects of specific interventions is dominated by studies of prospective new interventions compared to current practice [21]. The dental treatments (ART and CT) are daily performed during the normal clinical practice, but maybe with different materials (there is a large range of materials available in Brazilian market). In order to standardize the materials that will be used in this trial, we received a donation from the manufacturer. There is no conflict of interests, and the results will be published in good quality journals.

The patients of this trial will be children who study in the school where the dental office is located. Even it is not the best pragmatic way to perform the follow-up, the evaluation will be done by a single evaluator, in a school setting, in order to reduce drop-outs during the follow-up. This evaluation system is possible since we can locate the child aided by a national student’s data website [22].

Regarding our main outcome, to evaluate the survival rate of the ART and CT restorations, we chose the Roeleveld criteria [16], that allows splitting the evaluations in minor and major failure [23], therefore the survival of the tooth (in case of primary dentition) can also be calculated. The objective of a restoration is to provide the patient a condition for arresting caries lesion and avoid pulp problems or extractions. For that reason, studies should focus on the survival of the restored teeth and not remain limited to the minor failures of restoration survival [24, 25].

The ART is already well described in the literature, both in primary and permanent teeth [10, 26, 27] and well accepted by dentist due to its ease of use. In another hand, little is known about bulkfill composite resin, which can also be used as an aesthetic restoration and in one single increment. In that way, this pragmatic study will contribute to improve the knowledge about the ART and CT for restoring single or multiple surface carious lesions in primary and permanent dentition.

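### The Poisson analysis named for dentist preference cannot show which technique the ten dentists prefer

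*Protocol article*

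**What the plan says.** All places are in the protocol article.

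- **Aim.** Outcomes, item (IV), gives the purpose of the preference outcome: "Thus, we aim to identify which is the preferred procedure by professionals".
- **Analysis.** Data analysis has one sentence that names this outcome as something to be tested: "Poisson analysis will be used to assess the association between the treatment group, the preference of professionals and the cost of treatments". It gives neither a dependent variable nor a unit of analysis.
- **Design.** Study design states: "This is a pragmatic, two-arm, parallel group, patient-randomized trial which has 10 dentists as operators". Under Randomization the lists use permuted blocks of 2, 4 or 6 and are "stratified for operator (1–10), dentition (primary/permanent) and surface (single/multiple").
- **Timing.** Outcomes (IV) places the evaluation at the close of the operative phase, and later in the same item says: "This questionnaire will be administered before and after the research for the dentists".
- **Instrument.** Outcomes (IV) describes six items, adapted to compare composite resin with glass ionomer used in ART. The Discussion describes sixteen items that address "preference of amalgam or composite for posterior dental restorations, which can influence the quality of the restorations".
- **Other mention.** When Data analysis introduces the shared frailty model, it links the operator cluster effect to "its contextual variables (such as age, work experience and technique preference"). The hazard ratios are then to be adjusted by operator.

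**The concern.** The outcome asks a question about ten people: which of two techniques do they prefer? Treatment group is a property of the patient or tooth. Because the allocation is balanced within each dentist, knowing the arm of a tooth says almost nothing about the views of the dentist who treated it. An association between the two is close to absent by design, and a null result would be the same whether all ten dentists favoured ART or all ten favoured composite.

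At stake is a named secondary outcome. Followed literally, the plan would report a non-significant association that a reader could mistake for indifference between the techniques. The two descriptions of the questionnaire add a practical problem: the article does not fix how many items there are or which materials they compare, and amalgam is used in neither arm.

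**Working it through.** The plan states no sample size, power or expected result for preference, so there is no figure of its own to reproduce. The total of 1,214 teeth (304 + 278 + 304 + 328, Table 1) was computed for survival. It serves here only as the caseload over which the ten dentists are spread.

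**Step 1: what a group-preference association estimates.** Let dentist *j* treat *n_j* teeth, with *p_j* = 1 if that dentist prefers ART and 0 otherwise. Stratified blocks put about *n_j*/2 teeth in each arm. In either arm, the share of teeth treated by dentists who prefer ART is

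Σ *p_j*(*n_j*/2) / Σ (*n_j*/2) = Σ *p_j n_j* / Σ *n_j*.

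The arm cancels, so the between-arm ratio is 1. With equal caseloads, 8 of 10 dentists preferring ART gives 80 % in both arms, and 2 of 10 gives 20 % in both arms.

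**Step 2: check with incomplete blocks and unequal caseloads.** Simulation of 1,214 teeth, ten dentists with random caseloads, and blocks of 2, 4 or 6 within operator, dentition and surface:

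| True share preferring ART (assumed) | Mean between-arm ratio | 95 % simulation range |
|---|---|---|
| 20 % | 1.00 | 0.96 to 1.05 |
| 50 % | 1.00 | 0.97 to 1.03 |
| 80 % | 1.00 | 0.99 to 1.01 |
| 90 % | 1.00 | 0.99 to 1.01 |

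The statistic does not move with the quantity that the outcome is meant to identify.

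**Step 3: the other reading of the sentence.** If cost is the dependent variable, group and preference are explanatory terms. The preference coefficient then says whether treatment costs differ between dentists of different preference. It does not estimate how many dentists prefer which technique.

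**Step 4: what ten dentists can support.** Assume one binary answer per dentist (the item scoring is in Additional file 3, which is not shown). Exact two-sided binomial test against 50 %:

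- 8 of 10: 2 × (45 + 10 + 1)/1024 = 0.109
- 9 of 10: 2 × (10 + 1)/1024 = 0.021
- 10 of 10: 2 × 1/1024 = 0.002

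At least nine must agree for p < 0.05. Power is P(X ≥ 9) plus a negligible opposite tail: 15 %, 38 % and 74 % if the true preference is 70 %, 80 % and 90 % (assumed). The exact 95 % interval for 8/10 is 44 % to 97 %. For the before-after change, an exact paired test uses only dentists who switch. Five switches in one direction give 2 × (1/2)^5 = 0.063 and six give 2 × (1/2)^6 = 0.031, so at least six of the ten would have to change.

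**Step 5: effect on the main comparison.** In a simulation with ten operators, 30 teeth each and a true hazard ratio of 1.5, preference was made to depend on how each technique had fared in that dentist's hands. The treatment hazard ratio was 1.47 without and 1.48 with preference in the model.

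**The case against.** The strongest reply is that the Poisson sentence is ambiguous. It follows directly on the cost comparison, so cost may be the dependent variable, and then nothing is null by design. Treatment group might also mean the technique being rated. An article may leave a separate preference analysis to the full protocol or analysis plan. The ambiguity is real, and the absence of detail alone would be no finding. However, neither alternative makes the stated method answer the stated aim: with cost as the dependent variable preference is not estimated, and with paired ratings a within-dentist analysis of ten people would be needed, which the text does not say.

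Four stronger readings are tempting, and the documents do not support them.

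- *The questionnaire times contradict each other.* The end-of-phase evaluation can be the second half of the before-and-after scheme. The wording is loose and needs one clarifying line, because the close of the research could also mean the end of follow-up.
- *A preference answer given after treatment is entered in the survival model.* Data analysis lists preference only as an example of operator context and then adjusts by operator. It does not name preference as a fixed covariate.
- *Preference is to be tested against restoration quality.* The Discussion only remarks that it may have an influence. No such analysis, and no interaction between treatment and preference, is planned.
- *Copying ten answers onto tooth rows would produce false significance.* For the quoted group-preference association the error runs the other way. At 50 % preference and 607 teeth per arm, a naive standard error of the log ratio is √(2/607) = 0.057, a 95 % band of about 0.89 to 1.12. The simulated ratio stays within 0.97 to 1.03.

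**Conclusion.** The point holds in a limited form. The one analysis that names the preference outcome cannot identify the preferred procedure: read as a group-preference association it is expected to be null whatever the dentists think, and read as a cost model it leaves the outcome unestimated. The first conclusion rests on patient-level allocation, stratification by operator and preference being a property of the dentist, all of which the article supports. The exact-test figures rest on the added assumption of one binary answer per dentist.

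The conflicts over item count and over the materials compared are direct contradictions in the text, although the amalgam wording may have been carried over from the source questionnaire. This concerns a secondary outcome with ten respondents. A reader should not infer damage to the ART versus CT hazard ratio, which stratification by operator protects.

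**What to change.** 1. In Data analysis, name the dependent variable of the Poisson model and remove preference from that sentence as an outcome.
2. Analyse preference with the dentist as the unit (n = 10). Report each dentist's answers before and after and the paired change, descriptively with exact intervals, and use at most an exact paired test.
3. If preference is ever used as an explanatory variable in the survival or cost models, use only the pre-trial answer and label the result exploratory. A later answer may reflect how the technique performed.
4. In Outcomes (IV), state that the questionnaire at the end of the operative phase is the second of the two administrations.
5. Reconcile Outcomes (IV) and the Discussion on the number of items (six or sixteen) and on the materials compared (composite and glass ionomer, or amalgam and composite).

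The cost is wording and a simpler analysis, since administration before and after is already planned. The downside is that the preference outcome becomes openly descriptive.

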**Discussion:**

Our hypothesis is that despite similar expected effectiveness between ART using high viscosity GIC and conventional treatment using bulk fill composite resin when treating single or multiple-surface in posterior primary and permanent teeth, ART will present superior cost-effectiveness. The results of this trial will support decision-making by clinicians and policy makers.

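### The methods named for cost compare cost alone, so they cannot test the hypothesis that ART is the more cost-effective technique

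*Protocol article*

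**What the plan says.** The Discussion paragraph of the Abstract expects the two techniques to be similarly effective and adds that "ART will present superior cost-effectiveness". Outcomes lists "the evaluation of the cost-effectiveness of the two techniques applied" among the secondary outcomes; the primary outcome is restoration longevity.

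Part III of Outcomes explains how cost is built. Material prices are "converted in US Dollars and obtained by the mean values from different dental stores for the referred products". Professional cost comes from session time in hours, and the plan will "multiply it by the medium income of the dentist per hour as related by the Brazilian Ministry of Labor and Employment ($36.23"). Equipment depreciation is added at $1.81 per hour. On the comparison it says "The reference group to do the cost analysis will be the ART", and treatment times are recorded "in order to input the cost-effectiveness analysis of the methods used in the research".

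Data analysis then names two methods that involve cost. The first is a direct comparison of the arms: "The variance analysis will be used to compare groups in relation to the cost after determining data normality through the Kolmogorov-Smirnov test". The second sentence on cost relates three quantities to one another without naming the response: "Poisson analysis will be used to assess the association between the treatment group, the preference of professionals and the cost of treatments".

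The survival methods in the same section (Kaplan-Meier, log-rank, Cox, shared frailty) do not involve cost.

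**The concern.** Cost-effectiveness is a statement about cost and effect together. A test of mean cost answers whether one technique is cheaper, not whether it is better value. The distinction matters most when the cheaper technique also lasts less well, and that is where a policy maker would need the trial's answer.

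The Poisson sentence raises a second question. Cost here is a continuous money amount, not a count. A Poisson likelihood sets the variance equal to the mean, an equality that changes with the unit of money. If cost is the response and the default variance is used, the standard errors and p-values depend on whether cost is entered in dollars, cents or another currency.

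**Working it through.** **1. The plan's own figures.** No mean, SD, target difference or sample size is given for cost. The only design figure is the 1,214 teeth in Table 1, which is for survival. Freedman's log-rank formula, two-sided 5 %, 80 % power, reproduces its base sizes. For 93 % against 78 %: hazard ratio = ln 0.78 / ln 0.93 = 3.42; events = 7.849 × (4.42/2.42)² = 26.15; N = 26.15/0.145 = 180.3, so 181. In the same way 62 % against 82 % gives 165, and 41 % against 61 % gives 195. Multiplying by 1.4 and 1.2 gives 304.1, 277.2, 304.1 and 327.6, against the stated 304, 278, 304 and 328. The trial is therefore sized for tests of difference (15 or 20 points), not to show similarity.

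**2. Can similar effect be assumed, so that cost alone suffices?** Not from a non-significant log-rank test. Take primary multiple-surface teeth: 328 teeth, 164 per arm, with 41 % survival in both arms. Ignoring losses and clustering, SE of the difference = √(2 × 0.41 × 0.59 / 164) = 0.054, so the 95 % interval is ±1.96 × 0.054, about ±10.6 points. A zero estimate would still leave gains or losses of that size open.

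**3. What a cost test leaves undetermined.** Assume CT costs $2 more. The ratio is extra cost divided by the survival gain for CT.

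| Survival, CT minus ART | Result |
|---|---|
| +0.15 | 2/0.15 = $13 per additional surviving restoration |
| +0.05 | 2/0.05 = $40 per additional surviving restoration |
| 0 | no ratio; ART is simply cheaper |
| −0.15 | CT is dominated (dearer and fails more) |

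The cost p-value is the same in all four rows.

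**4. The Poisson model, if cost is the response and the variance is model-based.** The ratio of the Poisson SE to the true SE is √mean / SD. The real type I error at nominal 5 % is 2 × Φ(−1.96 × ratio). For an assumed mean of $20 and SD of $8: ratio = √20/8 = 0.559, type I error 27 %. By the same formula, in dollars:

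| CV (SD/mean) | mean $10 | mean $20 | mean $40 |
|---|---|---|---|
| 0.25 | 1.3 % | 8.0 % | 21.5 % |
| 0.4 | 12.1 % | 27.3 % | 43.8 % |
| 0.6 | 30.2 % | 46.5 % | 60.6 % |

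Simulation with 152 per arm (304/2) agrees within half a percentage point. All means and CVs are assumptions. As a plausibility check, at the plan's hourly rates of $36.23 + $1.81 = $38.04, $10 is 10/38.04 × 60 = 16 minutes of chair time and $40 is 63 minutes, before materials.

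**5. Unit dependence on one data set.** Simulated costs, 152 per arm, true means $20 and $22, CV 0.4:

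| Unit | Model-based Poisson z | p |
|---|---|---|
| hundreds of dollars | 0.41 | 0.68 |
| dollars | 4.10 | 0.00004 |
| cents | 41.0 | effectively 0 |

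The z value scales with the square root of the unit factor (4.10 × √100 = 41.0). In every unit, robust Poisson gave p = 0.026, quasi-Poisson 0.026 and analysis of variance 0.027.

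**The case against.** The strongest reply is that a cost-effectiveness analysis is planned. The Abstract lists it, and Outcomes gives the cost inputs and a reference group. A journal article can leave the estimator to a full protocol or analysis plan that is not shown. This stands as far as it goes: a reader might infer that cost and survival will never be combined, and the documents do not support that. The article does, however, go beyond silence. It publishes specific methods for cost, and these do not address its own hypothesis.

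Survival is also the primary outcome, with hazard ratios and intervals, so a technique that failed more often would be seen to do so. That limits the harm but does not supply a joint estimate.

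Other stronger readings also fail:

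- A reader might infer that both cost tests depend on the currency. Analysis of variance does not; nor does Poisson with robust or quasi-Poisson variance.
- A reader might call the Poisson intervals invalid outright. The text names neither the response nor the variance, and with a small mean and CV the test is conservative (1.3 % in the table). Cents show the mechanism only, since the plan uses US dollars.
- A reader might say that the cost analyses wrongly ignore clustering within child. The main Discussion section allows one cavity per child within a dentition-by-surface stratum and analyses strata separately, so this arises only if strata are pooled.
- Omitting operator is not clearly invalid either. Randomization is stratified by operator, so leaving out a common operator effect generally makes the comparison conservative.
- The article states no fallback if normality is rejected, but one could be specified elsewhere. How often the test would reject was not computed.

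**Conclusion.** The point holds for a secondary outcome. The two methods named for cost contain no measure of effect, and the difference tests used for survival cannot establish the similar effectiveness that would make a cost comparison sufficient. Followed as written, they cannot test superior cost-effectiveness. This conclusion rests on the text and needs no assumed figure.

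The Poisson problem is conditional on dollar cost being the response with default variance. Under assumed means of $10 to $40 and CVs of 0.25 to 0.6, type I error in dollars then lies between about 1 % and 60 %, and is about 27 % at a mean of $20 with an SD of $8. The primary survival analysis is not affected.

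**What to change.** In each of the four dentition-by-surface strata, report the difference in arithmetic mean cost (CT minus ART, as ART is the reference) jointly with the difference in 24-month restoration survival. Express the result as incremental cost per additional surviving restoration, or as net monetary benefit: λ × survival difference − cost difference, over a stated range of λ, the value placed on one surviving restoration. Net benefit is the steadier choice here, because the ratio is unstable when the survival difference is near zero, as the hypothesis expects. Take 95 % intervals from a bootstrap that resamples children within operator and arm. Report the mean difference whatever the Kolmogorov-Smirnov test shows.

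For regression on cost, name cost as the response and use a gamma model with log link, or Poisson with robust standard errors, with operator as a factor. Cluster by child only if strata are pooled.

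The downside is a little more analysis work. The trial already plans to collect the cost and survival data needed.
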